### Outcome Measures and Planned Analyses

#### Objective 1: Feasibility Outcomes Measures and Analysis: Trial Procedures

##### Overview

Quantitative and qualitative data will be used to assess and optimize the trial procedures and intervention component. Using the screening logs, consent outcomes, and the number of participants completing study procedures (onboarding, use of the technology longitudinally, PROMs at baseline and 3 months, and qualitative interview), we will create a study flow diagram to present descriptive statistics on the participant flow through the study, as per Figure 2.

##### Outcome 1: Recruitment Rates

The number of participants at each recruitment phase will be represented in the study flow diagram, as illustrated in Figure 2. The feasibility of recruitment will be assessed through the following indicators: the number of patients (1) attending the clinic, (2) screened by a clinician, (3) eligible to participate, (4) providing consent to contact, and (5) providing full consent. To determine the feasibility to progress to a larger study and full trial, we expect to reach a minimum of 70% of the recruitment target.

##### Outcome 2: Diversity of Recruited Sample

The clinical and demographic characteristics of those consenting to the study will be reported to evaluate the diversity of the recruited sample. Characteristics will include seizure type, age, gender, ethnicity, socioeconomic status, and digital literacy. This will help assess whether the recruitment approach was effective in enrolling a diverse sample and be used to inform a purposive recruitment strategy for a full trial if necessary.

##### Outcome 3: Barriers and Facilitators to Recruitment, With a Focus on Inclusive Trial Design for Those Underrepresented in Health Research

###### Quantitative Descriptive Statistics

The number of participants leaving the study at each point of the recruitment phase, along with their demographic characteristics and reason for withdrawal (were known), will be represented in the study flow diagram (Figure 2).

###### Stakeholder Consultations

If issues are identified during the recruitment phase, we will engage with people with epilepsy and the key members of the clinical and research teams to identify and document any barriers or problems related to recruitment. In response, practical, context-specific solutions aimed at improving recruitment processes will be developed and implemented collaboratively with the clinical team. This iterative approach will ensure that emerging challenges are addressed promptly and that recruitment strategies remain acceptable and feasible within the clinical setting. A full trial is unlikely to be feasible if we do not reach 70% of our recruitment target, and the qualitative data suggest that recruitment cannot be improved any further.

##### Outcome 4: Retention

To assess participant retention, the number of participants remaining in the study at each study procedure will be reported in the study flow diagram (Figure 2). Specifically, the following will be reported: the number of participants who completed (1) onboarding, (2) the technology deployment phase (either phase 1 or 2 version) in their lived context for up to 6 months, (3) PROMs at baseline and 3 months, and (4) a qualitative interview exploring their views of the technology (conducted with a subsample of 9-12 participants). To determine the feasibility to progress to a larger study and full trial, we expect to reach 80% retention at follow-up.

##### Outcome 5: Barriers and Facilitators to Retention, With a Focus on Inclusive Trial Design for Those Underrepresented in Health Research

The number and demographics of participants who leave the study, along with reasons for leaving (where known), will also be reported. If issues are identified during the retention phase, we will conduct PPI sessions with people with epilepsy to identify possible solutions to any barriers. A full trial is unlikely to be feasible if retention is <80%, and the qualitative data suggest that retention cannot be improved any further.

#### Objective 2: Feasibility Outcomes Measures and Analysis: Refining the Intervention

##### Outcome 6: Usability

###### Quantitative Use Metrics

Usability will be assessed through descriptive statistics of wear time (assessed using the presence of heart rate data), proportion of participants who complete the scheduled questionnaires at each time point. These quantitative indicators will offer insight into the feasibility and acceptability of both the data collection technology and associated data collection procedures.

To determine feasibility to progress to a larger study and full trial, we will consider the study feasible if at least 80% (≥48/60) of participants achieve an average wear time of ≥19 hours per day across the study period and a total average score of 5 on the MAUQ. This threshold was informed by established usability benchmarks for the System Usability Scale, which has been shown to be strongly correlated with the MAUQ [42].

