Objective 1 includes exploring the rate of recruitment and the diversity of the sample recruited. This will be used to inform a fully powered trial, for example, guiding the selection of additional sites and the length of the trial. This feasibility study will be used to determine the time frame needed to recruit 60 participants and the diversity of this sample. A sample size of 60 was selected to meet the requirements of objectives 2 and 3 (see below) and aligned with the typical sample size and recommendations for feasibility studies [31,32].Objective 2 focuses on refining the data collection technology of the seizure forecasting system. To do this, purposeful sampling will be used to identify 9-12 participants to invite them to take part in qualitative interviews to explore their experiences of using the MVP of the technology and identify any usability issues. Sampling for diversity will take place, with a focus on including individuals with lower digital literacy and from lower socioeconomic status groups. This is to ensure that the data collection technology is designed to include the needs of these groups to reduce the risks of digital exclusion and exacerbations of health inequalities. A sample size of 9-12 is considered sufficient to identify most usability issues in qualitative usability testing [33], ensuring a rich understanding of user experience and potential areas for improvement.Objective 3 seeks to add the data collected to the existing dataset to support the optimization of the seizure forecasting system. As the forecasting will be personalized and the system will be tailored to individual participants, the focus will be on obtaining accurate and continuous longitudinal data from each participant.

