#### Procedure 3: Qualitative Interview and Usability Questionnaire (Phase 2 Only)

At the end of the technology deployment, participants who used version 2 of the prototype (MVP) will be invited to participate in a qualitative interview with a member of the research team. These interviews will be scheduled for up to 60 minutes and use a semistructured topic guide (Multimedia Appendix 3) designed to explore participants’ views and experiences of using the technology.

Participants will also be asked to complete the mHealth App Usability Questionnaire (MAUQ), an 18-item questionnaire, which consists of 3 subscales that focus on ease of use (5 items), interface and satisfaction (7 items), and usefulness (6 items), rated on a 7-point Likert scale (1=strongly disagree to 7=strongly agree) [42].

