###### Quantitative User Experience (Phase 2 Only)

Usability will be assessed quantitatively by calculating the total and average scores of the MAUQ items.

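### The usability progression rule ties a phase-2-only questionnaire to a denominator of all 60 participants, and its printed count of 48 is not reconciled with an accepted recruitment minimum of 42

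*Protocol article*

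**What the plan says.** The rule stands under Outcome 6, Quantitative Use Metrics: "at least 80% (≥48/60) of participants achieve an average wear time of ≥19 hours per day across the study period and a total average score". The score meant is the MAUQ, and the value named is 5. It is one sentence with one subject, a share of participants printed both as a percentage and as a count out of 60, and two conditions joined by a conjunction.

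Three other places bear on it.

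- **Who gets the MAUQ.** The procedure is headed "Procedure 3: Qualitative Interview and Usability Questionnaire (Phase 2 Only") and the matching analysis "Quantitative User Experience (Phase 2 Only"). The Data Collection Technology overview gives each participant either the prototype or the MVP, according to when they join.
- **Recruitment.** Under Outcome 1, "we expect to reach a minimum of 70% of the recruitment target". The target is set in Sample Size: "This feasibility study will be used to determine the time frame needed to recruit 60 participants".
- **Phase split.** No section says how many of the 60 will be in each phase. The eligibility criteria require an iPhone for phase 2, while phase 1 admits owners of either type of smartphone.

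**The concern.** This is one of the protocol's stated thresholds for moving to a larger study and full trial, so it should give one clear answer once the data are in. As printed it leaves three things open.

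1. Phase 1 participants are in the denominator of 60 but will have no MAUQ score. If each counted participant must meet both conditions, they count as failures whatever their wear time.
2. A fixed count of 48 is larger than the smallest sample that the recruitment criterion accepts.
3. The MAUQ clause does not say whether 5 is a per-person score or a group mean, and it omits any ‘at least’.

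The risk is that good wear time and good usability still miss the threshold for structural reasons, or that the reading is chosen after the results are known. A prespecified progression criterion exists to prevent the second.

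**Working it through.** **Inputs.** Target 60 (Sample Size). Usability threshold 80%, printed as 48 of 60 (Quantitative Use Metrics). Recruitment minimum 70% of target (Outcome 1). MAUQ in phase 2 only (Procedure 3 and Quantitative User Experience headings). Number in phase 1, n1: not stated, so shown as a range.

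**Step 1: the plan's own figure.** 0.80 × 60 = 48. The printed count is correct for full recruitment, so there is no arithmetic slip.

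**Step 2: joint reading, 60 recruited.** Only phase 2 participants can meet both conditions, so the most that can qualify is 60 − n1, even with perfect wear and perfect MAUQ scores.

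| In phase 1 (n1) | Most who can qualify | Share of 60 | 80% reachable? |
|---|---|---|---|
| 0 | 60 | 100% | yes |
| 12 | 48 | 80.0% | only if all 48 qualify |
| 13 | 47 | 78.3% | no |
| 20 | 40 | 66.7% | no |
| 30 | 30 | 50.0% | no |
| 40 | 20 | 33.3% | no |

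The break point is n1 = 60 − 48 = 12. From 13 upward the rule fails by construction on this reading.

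**Step 3: the count against the recruitment minimum.** 0.70 × 60 = 42, and 42 < 48.

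- If the count governs, 48 is unattainable with 42 to 47 recruited (42/60 = 70% to 47/60 = 78.3% of target). At 48 recruited, all 48 must qualify.
- If the percentage governs, 0.80 × 42 = 33.6, so 34 of 42 suffice and there is no clash.

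**Step 4: does the percentage reading also cure Step 2?** No. At 42 recruited the joint reading needs 34 from 42 − n1, so n1 may not exceed 8. With 9 in phase 1 the ceiling is 33/42 = 78.6%. The phase problem and the count problem are separate and need separate answers.

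**Step 5: MAUQ as a group mean.** If the clause means that the phase 2 mean must reach 5, phase 1 participants no longer limit the result. Step 3 is unaffected, because the wear-time part still carries the 48/60.

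**The case against.** The strongest reply is that a sensible reader would not apply the rule so literally. The percentage comes first and the bracket merely works it out at the planned sample, so with 42 recruits one would look for 34. The MAUQ analysis computes total and average scores and is already confined to phase 2, so a group mean is a natural reading. Recruitment is planned to reach 60, and 70% is the least that the authors expect. The sentence also says when the study will be called feasible; it does not say that missing the threshold stops progression.

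Much of this stands. Each charitable reading is available, and together they make the rule workable. But they are two separate choices, and the protocol makes neither. The grammar of the sentence favours the joint per-participant reading. The bracket also carries its own inequality sign, so it can be taken as a requirement.

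Two stronger inferences should be resisted.

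- A reader might conclude that the rule cannot be met at all, or that the chance of passing is zero at 42 recruited. That follows only if the count overrides the percentage, or if the joint reading applies and phase 1 is large enough. The documents settle neither.
- A reader might also note that the retention criterion ("we expect to reach 80% retention at follow-up") leaves exactly 48 of 60, and infer that every retained participant must then reach 19 h/day. That needs a rule that those who leave count as wear-time failures, and the protocol states none. Use is for up to six months with monthly continuation, and someone who stops early may still have a qualifying daily average.

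**Conclusion.** The rule is wrong as written, in a conditional sense. It applies a phase-2-only measure to a denominator of all participants. Taken as a joint per-participant condition, it excludes everyone in phase 1 and cannot be satisfied with 13 or more of 60 in that phase. Its printed count is not reconciled with the accepted recruitment minimum: 48 against 42 if the count governs, 34 of 42 if the percentage governs.

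The size of the first problem depends on a phase split that the protocol does not give. The second depends on which of the two printed forms takes precedence. The missing ‘at least’ before the MAUQ score and the unnamed denominator are defects on any reading. The fault lies in how the decision threshold is specified, and it should be settled before any results are seen.

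**What to change.** Delete the 48/60 bracket and replace the sentence with two criteria:

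- **(a) Wear time.** At least 80% of a named denominator, for example the number actually onboarded, reach a mean of 19 hours per day or more. Recruited or retained would also serve as the denominator, provided that one is chosen and stated in advance.
- **(b) MAUQ.** The mean item score is at least 5 among phase 2 participants, with the phase 2 number as denominator.

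State that both must hold.

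The change needs protocol wording only and no new data. Its downside is that the MAUQ criterion then openly rests on the phase 2 participants alone. They are fewer than the full sample if anyone enters in phase 1, so the estimate is less precise.

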###### Quantitative User Experience (Phase 2 Only)

Usability will be assessed quantitatively by calculating the total and average scores of the MAUQ items.

###### Qualitative User Experience (Phase 2 Only)

Usability will also be assessed through qualitative interviews with participants who use the MVP version of the app. Interview data will be analyzed using thematic analysis to identify key themes related to the acceptability and feasibility of the app in its current form. In addition, tables of change will be used to systematically track suggested improvements and user feedback, highlighting specific areas where the app may require refinement. It is unlikely that a full trial will be feasible if the data suggest that the technology is not acceptable to users.

#### Objective 3: Refining the Algorithm Development

The longitudinal data on seizures and seizure precipitants (data collected from the data collection technology) will be added to the existing ATMOSPHERE dataset, shared with the modeling team to support the continued development of the seizure forecasting algorithm.

The modeling team will evaluate a combination of machine learning algorithms for seizure forecasting. Continuous physiological time series will be windowed (with segments ranging between 1 and 36 hours), and features will be calculated for each segment. Features will include statistical measures in the time domain (eg, mean, median, variance, skewness, and kurtosis) and the frequency domain (eg, mean frequency and peak frequency).

Features will be used to inform machine learning models to predict seizures in a period of time after each segment (forecasting window—ranging from 1 to 24 hours). Models will include 1-class support vector machine, isolation forest, and extreme gradient boosting. Model performance will be evaluated using well-established metrics such as accuracy, balanced accuracy, sensitivity, and specificity. We will also use a user-centered approach to evaluate performance, training the algorithm to minimize false positive or negative rates according to user preference. Model accuracy will be validated using a 5-fold cross-validation approach.

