## Introduction

### Background

Epilepsy is a chronic neurological disorder, which is characterized by recurrent and unpredictable seizures [1]. Although there have been significant advancements in treatment, up to one-third of people with epilepsy still experience recurrent seizures [2]. Epilepsy has a significant impact on the well-being and quality of life of people with epilepsy, in which fear and the unpredictability of seizures are considered greatly debilitating characteristics of the condition [3,4], with the unpredictability of seizures being identified as having the greatest impact on the lives of people with epilepsy [5]. To address the problem of unpredictability, technology to enable the prediction of seizures has been identified as a research priority by the UK Epilepsy Priority Setting Partnership [6]. To tackle this issue, there is a growing body of research investigating the potential for technology to provide seizure forecasts [7]. This technology holds promise for helping people with epilepsy take proactive steps to reduce the risk of injury and lessen the psychological burden caused by the unpredictability of seizures [8].

Current technologies for epilepsy have primarily focused on detection (identifying a seizure that is already happening) rather than predicting or forecasting future seizures. Electroencephalography (EEG) remains the leading method for monitoring brain signals to detect seizure activity. However, it is not well-suited for seizure forecasting, as EEG is impractical for long-term use outside clinical settings [9]. Ultra–long-term EEG monitoring is an alternative, which allows continuous EEG data capture outside clinical settings and in individuals’ real-world context. However, ultra–long-term EEG monitoring requires surgical implantation, and the associated risks and costs may limit its accessibility for many users [10]. Less invasive alternatives such as scalp EEG are available; however, their adoption is also limited due to low acceptance among users [4].

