#### Algorithm Development

As part of this project, we are developing a seizure forecasting algorithm that uses physiological time series data collected from a smartwatch. The algorithm calculates time- and frequency-domain feature statistics, which are combined with seizure timings, obtained from the companion app to train and test a combination of machine learning models to extract seizure propensity scores in different time scales. The data collected via the data collection technology will be added to the existing ATMOSPHERE dataset and used to refine and advance the seizure forecasting algorithm.

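### The forecast target does not separate follow-on from lead seizures, so where seizures cluster, part of the reported performance can come from recognising a recent seizure

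*Protocol article*

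**What the plan says.** The modelling outline is in the protocol article under Objective 3: Refining the Algorithm Development.

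- Input: "Continuous physiological time series will be windowed (with segments ranging between 1 and 36 hours), and features will be calculated for each segment".
- Target: "Features will be used to inform machine learning models to predict seizures in a period of time after each segment", with the "forecasting window—ranging from 1 to 24 hours".
- Scoring: "well-established metrics such as accuracy, balanced accuracy, sensitivity, and specificity", followed by "Model accuracy will be validated using a 5-fold cross-validation approach".

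The Algorithm Development section adds that the physiological feature statistics are "combined with seizure timings, obtained from the companion app to train and test a combination of machine learning models". Table 1 shows that the app records the timing and duration of each seizure.

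The outline sets no seizure-free interval before a target seizure, gives no rule for segments that contain a seizure or its aftermath, and names no simple comparator. On purpose, the Background section separates detecting a seizure already in progress from forecasting a future one, and describes the problem as unpredictability, "with the unpredictability of seizures being identified as having the greatest impact on the lives of people with epilepsy".

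**The concern.** If a participant has two seizures 15 h apart, the 24 h or 36 h segment ending just before the second one contains the first, with whatever heart-rate, movement and recovery signal it left. A model that has learned only that a seizure recently occurred will then be credited with forecasting the second. Such a model says nothing useful about seizures that arrive without a recent predecessor, which are the clearest case of the unpredictability that the Background section sets out to address.

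The route is plausible with wrist data. The Background section itself says that a wrist-worn device shows promise for seizure detection. Two of the three named model classes (1-class support vector machine and isolation forest) are anomaly detectors, to which a segment containing a seizure may look anomalous. At stake is how the reported metrics are read: they would mix forecasting skill with the degree of clustering among participants.

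**Working it through.** The article states no performance figure or target for the forecasting model, so there is nothing to reproduce. The check asks how well a rule with no forecasting skill for lead seizures would score under the stated design.

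**Inputs from the article.** Segment S of 1 to 36 h and window W of 1 to 24 h (Objective 3); at least two seizures expected per month, with no upper limit (Inclusion or Exclusion Criteria).

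**Assumptions.** Lead seizures arrive at random (Poisson), 2 per 30 days. Each seizure is followed by another 1 to 24 h later with probability p. The article gives no value for p, so it is varied: 0, 20, 40 and 60%. 400 simulated people, 180 days each, scored hourly.

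**Rule.** Alarm if and only if the preceding S hours held a seizure. Lead seizures occur independently of everything before them, so the rule has no skill for them. When the segment held no seizure, it never fires.

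**Formula.** Balanced accuracy = (sensitivity + specificity) / 2.

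**Step 1, no clustering, one patient, S = W = 24 h.** Alarm and target are independent. Sensitivity = 1 − exp(−2/30) = 0.065, specificity = exp(−2/30) = 0.935, balanced accuracy = (0.065 + 0.935)/2 = 0.50.

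**Step 2, with clustering.** Balanced accuracy by simulation, 2 lead seizures a month:

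| S, W | Earlier seizures visible to the features | p = 0 | 20% | 40% | 60% |
|---|---|---|---|---|---|
| 24 h, 24 h | all | 0.50 | 0.55 | 0.63 | 0.71 |
| 24 h, 6 h | all | 0.50 | 0.58 | 0.68 | 0.76 |
| 36 h, 1 h | all | 0.50 | 0.59 | 0.68 | 0.76 |
| 24 h, 24 h | half (assumed) | 0.50 | 0.53 | 0.57 | 0.63 |
| 1 h, 24 h | all | 0.50 | 0.51 | 0.51 | 0.52 |

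Repeat runs differ by about 0.01; for S = W = 24 h they span 0.55–0.56, 0.62–0.63 and 0.71–0.72. At p = 40% and S = W = 24 h, sensitivity is 0.32 and specificity 0.94: (0.32 + 0.94)/2 = 0.63. At 4 lead seizures a month, the values lie within about 0.04 of those shown.

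**Step 3, a different clustering model.** Let 25% of lead seizures start a cluster, with a mean of 2 follow-on seizures, at total rates of 2 to 30 a month. Balanced accuracy is then 0.54 to 0.57 (S = 36, W = 24) and 0.56 to 0.65 (S = 36, W = 1). With 80% starting a cluster and a mean of 4 follow-on seizures, it is 0.65 to 0.69 and 0.74 to 0.87. Both settings are assumptions.

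**Step 4, pooling without clustering.** Mix equal time from patients with 2 and 30 seizures a month, S = 36 h, W = 24 h. Alarm probabilities are 1 − exp(−0.1) = 0.095 and 1 − exp(−1.5) = 0.777. Target probabilities are 1 − exp(−0.067) = 0.065 and 1 − exp(−1) = 0.632.
- Pooled sensitivity = (0.095 × 0.065 + 0.777 × 0.632) / (0.065 + 0.632) = 0.71.
- Pooled specificity = 1 − (0.095 × 0.935 + 0.777 × 0.368) / (0.935 + 0.368) = 0.71.

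Balanced accuracy is 0.71 from rate differences between patients alone. This is a second reason to want a simple benchmark.

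**The case against.** The strongest reply is that this is an outline in a condensed article. The metric list is open, the Dissemination of Findings section says that the machine learning analysis is reported separately, and event definitions may be set in a modelling plan. That limits the point but does not remove it. The outline does fix the input, the target and example metrics, and as fixed they allow this credit. Separate reporting concerns publication and does not define the target.

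Four stronger readings are tempting, and the documents do not support them.

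- A reader might infer that all seizures are to be scored equally. The article does not say so; it only makes no distinction.
- A reader might infer that the shortcut reliably earns good performance. It does not. It earns nothing within a patient without clustering, almost nothing with 1 h segments, and at p = 40% its sensitivity is only 0.32. The simulated rule also sees every earlier seizure, whereas the planned features summarise whole segments and eligibility is not restricted to seizure types with a clear wrist signal.
- A reader might infer that a model could be carried into the full trial on follow-on seizures alone. The progression thresholds concern recruitment (Outcome 1), retention (Outcome 4), and wear time with the usability score (Outcome 6), not forecasting performance. Strengths and Limitations also calls for further testing once the algorithm is integrated.
- A reader might infer that follow-on seizures are not a legitimate target. The Introduction describes a risk score for seizures in the near future without limiting it to lead seizures, and a warning of a further seizure may be useful. This argues for reporting the two kinds separately, not for discarding one.

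**Conclusion.** The point holds as a conditional weakness. The target and the named metrics, as written, cannot show how much of the performance is forecasting of unexpected seizures and how much is recognition of a recent one.

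For a 24 h segment and a 24 h window, the no-skill rule reaches balanced accuracy of about 0.55 to 0.72 if 20% to 60% of seizures are followed by another within 24 h. That range is an upper bound in one respect: it assumes the features reveal every earlier seizure. If they reveal half, it falls to about 0.53 to 0.63. It does not bound every design, because shorter windows or heavier clustering give higher values. The size in this trial is unknown, since the article gives no clustering rate.

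**What to change.** In Objective 3: Refining the Algorithm Development, add a few lines:

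1. Keep all segments, and flag each one that contains a reported seizure.
2. Report performance for lead seizures (no reported seizure in the previous 24 h) separately from follow-on seizures, and repeat with 8 h and 48 h as sensitivity analyses.
3. Compare each model with a simple benchmark that predicts a seizure if one was reported in the segment, scored on the same data.
4. Leave flagged segments out only as a sensitivity analysis.

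On item 4, making exclusion the main analysis would give no main estimate for the period after a seizure and would discard much of the data from frequent seizures. With unclustered seizures and 36 h segments, the share of hours lost is 1 − exp(−1.5 × rate/30): about 53% at 15 seizures a month and 78% at 30.

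No new data are needed, because the app already records seizure timing and duration. The cost is fewer events in each stratum, wider intervals and possibly less favourable headline figures.
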